#### Anesthesia management

Standard intraoperative monitoring will include continuous electrocardiogram, pulse oxygen saturation, bispectral index (BIS), end-tidal partial pressure of carbon dioxide (P_ET_CO_2_), and invasive blood pressure. Anesthesia will be induced with intravenous etomidate (0.1–0.4 mg/kg), sufentanil (0.3–0.5 μg/kg), and cisatracurium (0.1–0.2 mg/kg). After tracheal intubation, anesthesia will be maintained with continuous intravenous propofol and remifentanil, which are adjusted to maintain the BIS values between 40 and 60. The lungs will be mechanically ventilated with a FiO_2_ of 50% and positive end-expiratory pressure set at 5 cmH_2_O. P_ET_CO_2_ will be maintained between 35 and 45 mmHg by adjusting the tidal volume to 6–8 ml/kg and a respiratory rate of 10–15/min. In cases where hemodynamic stabilization (blood pressure change within 20% of baseline) cannot be achieved despite adequate volume loading, norepinephrine infusion will be administered. If the surgical procedure requires muscle relaxation, an additional 4 mg of cisatracurium will be intravenously administered. The administration of anesthetics will cease once all surgical interventions are completed. Extubation will be performed when spontaneous breathes is adequate and the patient responds to commands. Following extubation, patients will be transferred to the post-anesthesia care unit (PACU). Patients will be discharged from the PACU when their Steward scores reach > 4. Other perioperative care will be provided according to the current ERAS practices for colon surgery [3].

For the prevention of postoperative nausea and vomiting (PONV), dexamethasone 5 mg will be administered intravenously to both groups after anesthesia induction. At the end of the surgery, ondansetron 4 mg will also be administered intravenously to both groups. For patients with severe PONV (three or more episodes of vomits or inability to have activities of daily living [26]), postoperative rescue antiemetic therapy with additional ondansetron 4 mg will be intravenously administered.

For postoperative analgesia, all patients will receive wound infiltration with 0.5% ropivacaine and an intravenous infusion of 50 mg flurbiprofen axentil at the end of the operation. The goal of postoperative analgesic management is to keep a pain score of less than 4 on a 0–10 point visual analog scale (VAS). After the discharge from the operating room, the same mode of patient-controlled intravenous analgesia (PCIA) with sufentanil (1 μg/ml) will be provided for up to 2 days in both groups. The PCIA pump will be programmed to allow a bolus of 2 μg, 15-min lockout, and 1-h limit of four doses. As part of the postoperative multimodal analgesia regimen, 50 mg of flurbiprofen axetil every 24 h and 1 g of acetaminophen every 8 h were also administered intravenously. Additional rescue medication is 50 mg tramadol administered intravenously whenever the VAS pain score is more than 4 points.

### Study outcomes

#### Primary outcome: Incidence of POD as assessed by 3-Minute Diagnostic Interview for Confusion Assessment Method (3D-CAM)

The primary endpoint of this study is the incidence of POD during the first 5 days after surgery. The assessment will be conducted daily using a Chinese version of 3D-CAM by a blinded investigator during face-to-face follow-up. The Chinese version of 3D-CAM has been demonstrated to have high sensitivity (82.6–93.8%) and specificity (96.7–98.1%), along with strong reliability and validity [27]. A positive result on the Chinese version of 3D-CAM is based on the presence of four criteria: (1) acute onset and fluctuating course; (2) inattention; (3) altered levels of consciousness; and (4) disorganized thinking. POD is defined if both criteria 1 and 2 are present, with at least one of criteria 3 and 4.

#### Secondary outcomes

Severity of POD assessed with Delirium Rating Scale-Revised-98 (DRS-R-98).

The severity of POD will be assessed daily using the Chinese version of DRS-R-98. This scale is composed of 13 items, and the total score ranges from 0 to 39 points [28]. The severity of POD for each patient will be determined based on the highest value recorded on the scale during the first 5 postoperative days.

(2)Duration of POD assessed by 3D-CAM.

Duration of POD will be measured in terms of the number of days from the onset of delirium symptoms to the resolution of these symptoms.

(3)Subtype of POD assessed with the Richmond Agitation and Sedation Scale (RASS).

The subtype of POD will be defined based on the RASS score as follows [29]: hyperactive type, RASS score > 0; hypoactive type, RASS score < 0; mixed type, the hyperactive and hypoactive types occur alternately.

(4)Postoperative pain level during rest and physical activity measured with a 0–10 point VAS.

Postoperative pain level during rest and physical activity will be evaluated daily using the VAS [30]. Furthermore, the dosages of all opioids for postoperative pain control will be recorded and converted to morphine milligram equivalents.

(5)Sleep disturbance assessed with PQSI.

Patients with POD often experience pre- and postoperative sleep disturbances [31]. Therefore, PSQI scores will be determined at baseline and during the first 5 postoperative days. A sleep disorder will be defined if the PSQI score is higher than 5.

(6)Intraoperative relevant parameters.

Various intraoperative parameters, including blood loss, fluid volume, hypotension (defined as mean arterial pressure (MAP) below 65 mm Hg), hypertension [defined as systolic blood pressure (SBP) and/or diastolic blood pressure (DBP) greater than 30% of their baseline values, or SBP is ≥ 140 mmHg and/or (DBP) is ≥ 90 mmHg, tachycardia (defined as heart rate > 100 bpm), bradycardia (defined as heart rate < 50 bpm), arrhythmia and operation time will be recorded.

(7)Postoperative non-delirium complications and economic parameters.

The postoperative non-delirium complications, such as postoperative nausea and vomiting, pulmonary infection, myocardial infarction, and renal failure, will be documented. Economic parameters, including hospital stays, total hospital costs, and anesthesia-related expenditures, will also be recorded.

(8)Tissue/blood sampling and laboratory parameters.

Given the potential correlation between the inflammatory response and POD [32], the study will examine the activation of microglial cells, the levels of inflammatory cytokines including tumor necrosis factor (TNF-α) and interleukin-6 (IL-6) in the colon tissues for all patients. Additionally, the blood samples will be collected at baseline, after anesthetic induction, postoperative days 1 and 3, and will be analyzed for markers of glial injury including serum protein S100β, neuron-specific enolase (NSE), inflammatory cytokines (TNF-α and IL-6), and the indicators of intestinal permeability including serum D-lactic acid (D-LAC) and diamine oxidase (DAO).

### Statistical analysis

Statistical analysis will be conducted using SPSS 23.0 software by qualified statisticians from the clinical research center of Beijing Friendship Hospital. Due to the need for repeated evaluations of patients during the trial process, which may affect patient compliance, we will analyze the outcomes using both the Full Analysis Set (FAS) and the Per-Protocol Set (PPS) and compare the results from both analyses. The FAS will include all participants who are randomized according to the intention-to-treat principle, regardless of whether they strictly adhered to the trial protocol. Missing values in the FAS will be processed using the Last Observation Carried Forward (LOCF) method. The PPS will be defined as the population who strictly followed the trial protocol. This dual approach ensures a comprehensive assessment of xenon’s effectiveness, considering both generalizability and protocol adherence.

All statistical tests will be 2-sided, and a *p* value < 0.05 will be considered to indicate statistical significance. The choice of statistical tests will depend on the types and distributions of the parametric data.

The primary outcome, incidence of POD within the first postoperative 5 days, will be analyzed using *χ*^*2*^ tests.Categorical secondary outcomes, including subtypes of POD; the rates of intraoperative hypotension, hypertension, tachycardia, bradycardia, and arrhythmia; postoperative sleep disorder; and non-delirium complications, will also be analyzed with the* χ*^*2*^ test.Parametric data will also be tested for homogeneity of variance by using the Levene median test. If the data follow a normal distribution and exhibit homogeneity of variance, they will be expressed as mean ± standard deviation and compared between groups using the *t*-test. When data do not meet the criteria for normal distribution or have uneven variances, they will be presented as median (interquartile range) and compared between groups using the Mann–Whitney *U* test.The within-group comparisons of data at multiple time points will be performed with the repeated-measures ANOVA.Time-to-event outcomes, such as the duration of POD and hospital stay, will be analyzed using the log-rank test.The logistic regression analysis will be utilized to examine the factors influencing the primary outcome between groups while controlling for covariates, such as preoperative frailty score, postoperative pain, and pre- and postoperative sleep disturbances.

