### Sample size calculations

The primary endpoint is the incidence of POD in the first 5 postoperative days. Based on the unpublished retrospective observational study enrolled 49 patients in Beijing Friendship Hospital, Capital Medical University, China, the incidence of POD in elderly patients undergoing elective laparoscopic radical colectomy was 35.7%, while it was 14.3% in the other elective laparoscopic surgery. We hypothesize that short-term inhalation of xenon during anesthesia can reduce the incidence of POD down to the same level as patients in the other elective laparoscopic surgery. To achieve a power of 80% with a two-tailed alpha of 0.05, 61 patients are at least needed in each group. Considering 8% potential dropouts or losses to follow-up, we will enroll 66 patients in each group, leading to a total sample size of 132 patients.

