### Standard procedure

#### Preoperative evaluation

All patients will be visited and examined the day before surgery. Demographic data including education levels, medical history, current medications, and results of physical and laboratory examinations will be collected and analyzed. Signs and symptoms of preoperative cognitive impairments will be assessed preoperatively with MMSE [22]. Frailty of the patients at baseline will be measured by means of a multidimensional frailty score [23]. Preoperative sleep disturbances at base will be calculated with PSQI [24].

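### The primary delirium comparison is a valid but unadjusted chi-square test; baseline covariates already collected could add power, by an amount that depends on their unknown prognostic strength

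*Protocol article*

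**What the plan says.** The endpoint is binary: "The primary endpoint is the incidence of POD in the first 5 postoperative days". For its analysis the Statistical analysis section says "The primary outcome, incidence of POD within the first postoperative 5 days, will be analyzed using" chi-square tests and names no covariate.

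The Preoperative evaluation section has every patient seen the day before surgery. Demographics, education and MMSE are recorded. "Frailty of the patients at baseline will be measured by means of a multidimensional frailty score", and PSQI is taken as well. The Background lists preoperative cognitive impairment and frailty among the factors that predispose to POD and says that such factors build up with age.

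One adjusted analysis is planned. The last item of the Statistical analysis section is a logistic regression on factors influencing the primary outcome between groups, "while controlling for covariates, such as preoperative frailty score, postoperative pain, and pre- and postoperative sleep disturbances". The Discussion describes the same model as a study of high-risk factors.

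The Blinding and randomization section gives a 1:1 ratio and names no stratification factor.

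**The concern.** The confirmatory test makes no use of baseline information that the trial will hold on everyone. When baseline variables predict a binary outcome, a treatment test adjusted for them has more power at the same sample size.

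The logistic regression does not fill this gap. Its covariate list is open, and it is presented as a study of influencing factors rather than as the treatment comparison. It also conditions on postoperative pain and postoperative sleep. Both are measured after randomisation, over the same days as POD, so xenon or POD itself could affect them. The group coefficient from that model is therefore not a clean treatment effect. As the article stands, no baseline-only adjusted treatment estimate is described.

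At stake are a few points of power in a trial sized close to 80%, with about 30 to 33 expected events.

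**Working it through.** **Inputs from the Sample size calculations section.** Rates: "the incidence of POD in elderly patients undergoing elective laparoscopic radical colectomy was 35.7%, while it was 14.3% in the other elective laparoscopic surgery". The second figure is the target under xenon. Size: "To achieve a power of 80% with a two-tailed alpha of 0.05, 61 patients are at least needed in each group". An 8% allowance for losses then brings this to 66 per arm.

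**1. Reproduce the plan's figure.** Normal approximation, unpooled variance:

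n = (1.96 + 0.8416)² × [0.357 × 0.643 + 0.143 × 0.857] / (0.357 − 0.143)² = 7.849 × 0.3521 / 0.0458 = 60.35, rounded up to 61.

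This matches the plan, so the trial is sized for the unadjusted comparison. The pooled-variance formula, which corresponds to the Pearson chi-square test, gives 64. By that formula power is 78.6% at 61 per arm and 81.8% at 66. With 8% lost, 66 × 0.92 = 60.7 per arm remain.

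**2. Expected events.** 61 × (0.357 + 0.143) = 30.5, and 66 × 0.500 = 33. Only a few covariates can be carried.

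**3. Power with adjustment, 61 per arm.** Prognostic strength is an assumption, because the documents give no odds ratio, AUC or similar figure. Marginal rates were held at 35.7% and 14.3%. The unadjusted test is the Pearson chi-square without continuity correction.

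| Assumed baseline strength | Chi-square | Adjusted | Difference (points) |
|---|---|---|---|
| One score, AUC 0.50 (OR 1.00 per SD) | 79.4% | 79.4% | 0.0 |
| One score, AUC 0.64 (OR 1.65) | 80.0% | 81.3% | 1.3 |
| One score, AUC 0.69 (OR 2.12) | 79.6% | 82.9% | 3.3 |
| One score, AUC 0.74 (OR 2.72) | 78.9% | 84.3% | 5.4 |
| One score, AUC 0.78 (OR 3.49) | 80.0% | 87.9% | 7.9 |
| One score, AUC 0.81 (OR 4.48) | 79.5% | 90.1% | 10.6 |
| Three covariates, AUC 0.66 | 78.9% | 81.0% | 2.1 |
| Three covariates, AUC 0.72 | 80.1% | 83.9% | 3.8 |
| Three covariates, AUC 0.77 | 80.4% | 87.0% | 6.6 |

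The one-score rows use 4,000 trials each and a likelihood-ratio test (simulation error about √(0.8 × 0.2 / 4000) = 0.6 points per figure). The three-covariate rows use 10,000 trials each and a score test.

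A further three-covariate simulation set the log odds ratio per SD of the combined score at 0, 0.5, 0.75, 1 and 1.25. It gave about 78%, 82%, 82%, 85% and 87% adjusted, against about 80% unadjusted. Three uninformative covariates can therefore cost a point or so.

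**4. Power at the enrolled 66 per arm (one score).** Unadjusted about 82 to 84%. Adjusted 83.9%, 84.8%, 86.6%, 88.1%, 89.1% and 91.8% at AUC 0.50, 0.64, 0.69, 0.74, 0.78 and 0.81.

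**5. Type I error of the adjusted test, 61 per arm.** 4.8 to 5.6% with one score (chi-square 4.4 to 5.3%). With three covariates it was 5.0 to 5.5% in one simulation and 5.4 to 6.2% in the other (chi-square 4.8 to 5.8% in the latter).

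**The case against.** The strongest reply is that nothing here is wrong. A chi-square test is valid for a randomised binary endpoint, it agrees with the sample size calculation, and its 5% error rate already allows for chance baseline imbalance. All of that stands. A reader might infer that the trial is biased, or underpowered because it does not adjust. The documents support neither reading: the trial has about its planned power without adjustment.

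A reader might also infer that strong predictors are being ignored. The documents do not show this. They list risk factors without any measure of strength. The Inclusion criteria limit age to 65 to 80, and the Exclusion criteria remove patients with cognitive impairment on MMSE. Both restrictions tend to weaken those two covariates, so the gain may be close to zero.

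Nor is adjustment free. It needs an amendment, it changes the effect measure unless a standardised risk difference is reported, and the adjusted test may run slightly above 5%.

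Finally, a logistic regression that includes preoperative frailty and sleep is already planned, and its final covariate list may properly be left to an analysis plan. That is fair as to the open list. It does not answer the point, because the variables the article does name include two postoperative ones, and the primary test is stated as unadjusted.

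**Conclusion.** The point holds as a loss of efficiency. The article commits the primary comparison to an unadjusted test, while plausible baseline predictors are collected on all patients and the only adjusted model is unsuitable for estimating the treatment effect.

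At 61 per arm, against about 80% unadjusted, the gain is:

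- about zero, or a point or so lost, if the covariates are uninformative;
- about 3 to 5 points at AUC about 0.69 to 0.74;
- about 7 to 10 points only at AUC about 0.77 to 0.81.

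These figures rest on the plan's own rates of 35.7% and 14.3% and on an assumed prognostic strength that the documents cannot settle. The change is worth making, but the planned analysis remains valid without it.

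**What to change.** Amend the plan before the unblinded interim look described under Data management, which falls at nearly half of the cases:

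- Make the primary analysis a logistic regression of POD on group plus two or three named baseline covariates, for example frailty score, age, and baseline MMSE or PSQI.
- Include no postoperative variable in this model.
- Report a standardised risk difference with 95% CI as the effect estimate.
- Keep the chi-square test as supportive.
- Present any regression with postoperative pain or sleep as exploratory, not as an estimate of the treatment effect.

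No new patients or measurements are needed. The costs are a protocol amendment while recruitment is under way (30 patients at the time of the article), a ceiling of about three covariates with 30 to 33 expected events, and a conditional odds ratio that differs from the crude one, which the standardised risk difference resolves. The adjusted test's type I error was about 5 to 6% in simulation and should be checked for the chosen test and covariates before the choice is fixed.

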This study aims to validate the hypothesis that a short xenon inhalation during anesthesia will reduce the occurrence of POD in elderly patients undergoing laparoscopic radical colectomy. Positive results could guide anesthesiologists in selecting appropriate anesthesia for specific patient subgroups, potentially justifying the cost associated with xenon administration to benefit this high-risk population.

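### The plan moves normal data with unequal variances from the t-test to Mann-Whitney, which does not correct for unequal spread; separately, costs need a comparison of means

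*Protocol article*

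**What the plan says.** The Statistical analysis section sets a two-step rule for continuous outcomes. First comes a variance check: "Parametric data will also be tested for homogeneity of variance by using the Levene median test". The t-test then depends on two conditions at once: "If the data follow a normal distribution and exhibit homogeneity of variance, they will be expressed as mean ± standard deviation". If either fails, the summary and the test both change: "When data do not meet the criteria for normal distribution or have uneven variances, they will be presented as median (interquartile range"), compared by Mann-Whitney. No unequal-variance form of the t-test is named.

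Under Secondary outcomes, item (7), the article adds: "Economic parameters, including hospital stays, total hospital costs, and anesthesia-related expenditures, will also be recorded". Hospital stay has its own method ("Time-to-event outcomes, such as the duration of POD and hospital stay, will be analyzed using the log-rank test"). The two cost variables have none, so they fall under the general rule. The Discussion says what a positive result might support: "potentially justifying the cost associated with xenon administration to benefit this high-risk population".

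**The concern.** There are two separate problems.

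**The remedy does not match the fault.** The usual null distribution of Mann-Whitney is derived for two identical distributions. If the arms have the same mean and median but different spread, the variance used for the rank statistic is wrong, just as the pooled variance can be wrong for the ordinary t-test. Normal data gain nothing from the switch and lose the mean difference.

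**Costs lose the mean.** Cost data are commonly skewed, so the non-normality condition would usually send them to a median and a rank test. Mean cost per patient multiplied by the number of patients gives total expenditure; the median does not. If costs are to inform whether xenon is worth its price, the mean difference is the relevant quantity.

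At stake are the p values and summaries of some secondary outcomes. The primary outcome, delirium incidence, is tested by chi-square and is not touched.

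**Working it through.** **Inputs.** From the article: 1:1 allocation (Blinding and randomization), 66 enrolled per arm (Sample size calculations), two-sided 0.05 (Statistical analysis). The arm size can be reproduced: the unpooled two-proportion formula with 35.7% v 14.3% and 80% power gives 60.35, so 61, and 61 × 1.08 = 65.9, so 66. Assumed, because the article gives no SDs: SD ratios of 1.5 to 4 for normal data, log-SDs for costs, and 66 v 50 as an example of unequal analysed arms (for instance in the per-protocol set).

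**1. Mann-Whitney, normal data, equal means.** Let arm X have SD 1 and size m, and arm Y have SD r and size n. Write Var(U) = mn × V.

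- Variance the test assumes: V₀ = (m + n + 1)/12.
- True variance: V = 1/4 + [(n − 1)·arcsin(1/(1 + r²)) + (m − 1)·arcsin(r²/(1 + r²))]/(2π).
- Rejection rate ≈ 2Φ(−1.96/√(V/V₀)).

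For m = n = 66 and r = 2: V₀ = 133/12 = 11.083; V = 0.25 + 65 × (0.2014 + 0.9273)/6.2832 = 11.926; V/V₀ = 1.076; 1.96/√1.076 = 1.89; rejection rate 5.9%.

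The other cases, with simulation (20,000 trials per scenario, simulation error up to about ±0.4 points):

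| Arms (X/Y) | SD ratio r | V/V₀ | Mann-Whitney, formula | Mann-Whitney, simulated | Welch, simulated |
|---|---|---|---|---|---|
| 66/66 | 1.5 | 1.028 | 5.3% | 5.2% | 5.0% |
| 66/66 | 2 | 1.076 | 5.9% | 5.8% | 5.1% |
| 66/66 | 3 | 1.161 | 6.9% | 6.8% | 4.9% |
| 66/66 | 4 | 1.222 | 7.6% | 7.4% | 5.1% |
| 66/50, larger SD in smaller arm | 2 | 1.171 | 7.0% | 7.3% | 5.3% |
| 66/50, larger SD in smaller arm | 3 | 1.294 | 8.5% | 8.5% | 5.1% |
| 50/66, larger SD in larger arm | 2 | 0.981 | 4.8% | 4.7% | 5.0% |
| 50/66, larger SD in larger arm | 3 | 1.028 | 5.3% | 5.2% | 4.9% |

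At 66/66 the ordinary pooled t-test also holds its level (5.2% at ratio 2, 5.0% at ratio 3), so in equal arms the switch makes matters slightly worse. At 66/50 the pooled t-test gives 7.5% and 8.2%, about as far off as Mann-Whitney. The switch does happen: at a ratio of 2 with 66 per arm, the Levene median test rejects in 99.9% of trials.

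**2. Costs, log-normal illustration.** The mean is exp(μ + σ²/2), so equal means require μ = −σ²/2. With log-SDs 0.5 and 0.75, the medians are exp(−0.125) = 0.882 and exp(−0.281) = 0.755, a ratio of exp(0.15625) = 1.17. Mann-Whitney rejects in about 28% of trials and Welch in about 5.3%. In the opposite case, with equal medians and log-SDs 0.4 and 0.8, the mean is exp((0.64 − 0.16)/2) = 1.27 times higher in one arm; Mann-Whitney rejects 5.9% and Welch 39%. The rank test follows the medians and not the mean cost, in both directions.

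**3. What Welch costs if used everywhere.** Log-normal data, equal log-SDs, a shift of 0.5 log-SD, 66 per arm: power is 79% (Mann-Whitney) v 76% (Welch) at log-SD 0.5, 79% v 70% at 0.75, and about 79% v 62% at 1.0.

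**The case against.** The strongest reply is that the harm is small and not always in one direction. In near-equal arms it is under one point at an SD ratio of 2, and nothing in the article suggests ratios of 3 or 4. If the more variable arm is the larger, the rate is at or just below 5%. And if xenon has no effect at all on an outcome, randomization gives both arms the same distribution and Mann-Whitney holds its level. All of this stands. A reader might infer that secondary p values are generally too small under this plan; the article does not support that.

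A reader might also take the 28% as a false-positive rate. It is not one for the summary the plan reports: the medians truly differ by 17% in that scenario, and the spreads are assumed. It shows only that the test does not address mean cost.

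The two problems also have different routes. Skewed costs would mostly reach Mann-Whitney through non-normality, so repairing the unequal-variance branch would not change their analysis. Nor does the article name mean cost as its target: costs are listed as recorded, no cost-effectiveness analysis is described, and the remark on justifying cost is in the Discussion. This limits the cost point to a recommendation tied to that stated use.

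Finally, Welch for every continuous outcome would be a poor exchange. The plasma and tissue markers may well be skewed, and there Welch loses power.

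**Conclusion.** The point holds in a narrow form. The rule sends normal data with unequal variances to a test that does not correct for unequal variances. With 66 per arm the excess over 5% is about 0.2, 0.8, 1.8 and 2.4 points at assumed SD ratios of 1.5, 2, 3 and 4. It rises to roughly 2 to 3.5 points at ratios 2 to 3 when the more variable arm is the smaller (66 v 50), and largely vanishes when it is the larger. Welch stays near 5% in all these cases.

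On costs, the rule would usually yield a median and a rank test, which do not answer the question of mean cost raised in the Discussion. The size of that discrepancy depends on spreads the article does not give.

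Only continuous secondary outcomes are affected. The primary analysis and the sample size stay as they are. This is a desirable improvement, not a threat to the trial's main conclusion.

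**What to change.** Amend the Statistical analysis section in three respects:

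1. For approximately normal data with unequal variances, use Welch's t-test and report the mean difference with a 95% CI.
2. Keep Mann-Whitney for ordinal scores and for skewed outcomes such as the biomarkers. Do not extend Welch to all continuous outcomes.
3. For total hospital costs and anesthesia-related expenditures, report the difference in mean cost with a bootstrap or Welch 95% CI. Medians and quartiles can be shown alongside as description.

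This changes wording only: no extra data and no change in sample size. Trial status reports 30 participants recruited, so it can be settled well before the final analysis. The downside is a little more analysis work and a wider interval for skewed costs.

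### Repeated-measures ANOVA is confined to within-group comparisons and the between-arm tests use no baseline covariate, so collected information on repeated secondary outcomes goes unused

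*Protocol article*

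**What the plan says.** All statements are in the protocol article; no separate SAP is shown.

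- **Longitudinal method** (Statistical analysis): "The within-group comparisons of data at multiple time points will be performed with the repeated-measures ANOVA". It is the only method named for several time points, and no arm-by-time term is mentioned.
- **Between-arm tests, continuous data** (same section): if normal with equal variances, "they will be expressed as mean ± standard deviation and compared between groups using the" t-test; otherwise "compared between groups using the Mann–Whitney" U test. Neither is given a baseline covariate.
- **Between-arm test for sleep, as a category** (same section): "postoperative sleep disorder; and non-delirium complications, will also be analyzed with the" chi-square test. Sleep disorder means a PSQI score above 5.
- **The only covariate-adjusted model** is a logistic regression for delirium, "while controlling for covariates, such as preoperative frailty score, postoperative pain, and pre- and postoperative sleep disturbances".
- **Blood markers** (Secondary outcomes, item 8): "the blood samples will be collected at baseline, after anesthetic induction, postoperative days 1 and 3". They are S100β, NSE, TNF-α, IL-6, D-LAC and DAO.
- **PSQI** (Secondary outcomes, item 5): "PSQI scores will be determined at baseline and during the first 5 postoperative days".
- **Pain** (item 4) is scored daily after surgery; no preoperative score is described. Colon-tissue markers are not described as repeated.

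The Background gives the purpose of the markers: to explore how xenon might lower delirium.

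**The concern.** What xenon does is a question about the difference between arms. A repeated-measures ANOVA run within an arm tests whether values change over time in that arm. Surgery can change them in both arms, so the result does not bear on xenon, and setting two such p values side by side does not test a difference.

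The comparison that does address xenon is left to tests that, as stated, do not use the baseline value. That value is already collected for every blood marker and for the PSQI. At stake is the precision of the mechanistic and sleep results, and the clarity of what will count as evidence of an effect on them.

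**Working it through.** **Plan's own figure.** The protocol gives no figure for the repeated outcomes. Its 61 evaluable patients per arm is for delirium (35.7% v 14.3%, two-sided 0.05, 80% power). With unpooled variance, (1.960 + 0.842)² × (0.357 × 0.643 + 0.143 × 0.857) / 0.214² = 60.35, so 61. It reproduces, and n = 61 per arm is used below.

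**1. Precision forgone between arms.** Adjusting for a baseline with correlation ρ to follow-up multiplies the variance by 1 − ρ². The documents give no ρ, so 0.3, 0.5 and 0.7 are assumptions. Power for a difference of d SD (normal approximation) is Φ(d√(n/2)/√(1 − ρ²) − 1.96).

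For d = 0.5 and n = 61, d√(n/2) = 0.5 × 5.523 = 2.761.

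- Unadjusted: Φ(2.761 − 1.96) = Φ(0.80) = 78.9%
- ρ = 0.5: Φ(2.761/0.866 − 1.96) = Φ(1.23) = 89.0%

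The detectable difference at 80% power is 2.802 × √(2(1 − ρ²)/61). The unadjusted sample size with the same precision is 61/(1 − ρ²).

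| | Variance cut | Power, 0.5 SD | Power, 0.4 SD | Detectable at 80% | Equivalent n per arm |
|---|---|---|---|---|---|
| Unadjusted | – | 78.9% | 59.8% | 0.51 SD | 61 |
| ρ = 0.3 | 9% | 82.5% | 63.9% | 0.48 SD | 67 |
| ρ = 0.5 | 25% | 89.0% | 72.3% | 0.44 SD | 81 |
| ρ = 0.7 | 49% | 97.2% | 87.1% | 0.36 SD | 120 |

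**2. Within-arm p values read as a contrast.** If the arms are identical and each has probability p of a significant within-arm test, exactly one is significant with probability 2p(1 − p). The maximum is 50%, at p = 0.5.

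Simulation: 4,000 trials per setting, 61 per arm, four time points, normal data, common correlation 0.5 (assumed), and the same shift at the last two times in both arms.

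| Common shift (SD) | Within-arm power | Only one arm significant |
|---|---|---|
| 0 | 6% | 10% |
| 0.15 | 26% | 37% |
| 0.2 | 41% | 48% |
| 0.25 | 61% | 48% |
| 0.3 | 79% | 33% |
| 0.4 | 97% | 6% |

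With a larger shift both arms are nearly always significant and the discordance goes towards zero.

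**3. Validity of the stated between-arm test.** In the same simulation the unadjusted t-test at the last time point rejected in 4.5% to 5.4% of trials, so it keeps its 5% level.

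**The case against.** The strongest reply is that the plan does compare the arms. The t, Mann–Whitney and chi-square tests are listed beside the within-group ANOVA, not replaced by it, and randomization makes them valid without adjustment. That stands: the loss is efficiency, not validity.

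A reader might infer that the trial will claim a xenon effect when one arm changes significantly and the other does not. No section says so, and describing a time course within each arm is no error. Nor is a discordance near 50% to be expected: it is the ceiling, and a large surgical response would take it close to zero.

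A reader might also infer that baseline values are never used. That is too broad. Baseline is one of the sampling times and would naturally enter the within-group ANOVA, and preoperative sleep disturbance is a covariate in the delirium model. Pain has no described baseline to adjust for. The section does not list which outcomes the ANOVA covers; blood markers, PSQI and pain are inferred from their schedules.

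The plan also moves to Mann–Whitney "When data do not meet the criteria for normal distribution or have uneven variances". A reader might call this a serious error, since that test need not hold its level for equal locations with unequal spreads. Three simulations with normal data at 61 per arm gave type I error of 5.3–5.9% at an SD ratio of 2, 6.3–7.0% at 3 and 7.8–8.2% at 5. Nothing in the protocol suggests a three- to fivefold SD difference between randomized arms, so this is minor and does not carry the point.

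Finally, model terms for secondary outcomes are often left to an SAP. That would answer a complaint about missing detail. It does not answer a stated sentence that confines the longitudinal method to within-group comparison.

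**Conclusion.** The point holds as a matter of efficiency and clarity on secondary outcomes. The named longitudinal method yields no arm contrast, and the between-arm tests for continuous outcomes, though valid, name no baseline covariate where one is collected. The variance reduction given up is 9% to 49% for ρ from 0.3 to 0.7; at ρ = 0.5 it equals raising the evaluable number from 61 to 81 per arm. The size depends on ρ, which the documents do not give and which may differ by marker. The possible misreading of within-arm p values is conditional: about 0% to 50% discordance between identical arms, governed by a common change that the documents do not quantify. The colon-tissue markers, the primary chi-square test and the sample size are not touched. It should be changed, but the trial's main conclusion does not depend on it.

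**What to change.** Replace the within-group ANOVA sentence as follows.

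- For each repeated blood marker and for the PSQI score, fit one mixed model with arm, time and arm-by-time, adjusted for the patient's baseline value, on the log scale for skewed markers. If the PSQI turns out to have a single postoperative score, this reduces to analysis of covariance.
- For daily VAS pain, use the same model without the baseline term.
- Report the between-arm difference at each time with a 95% CI.
- State that within-arm changes are descriptive and are not evidence of a xenon effect.

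The cost is a short change of wording and slightly more programming in SPSS; no new data or visits are needed. It should be settled before the unblinding and interim analysis that the Data management section plans at about half of the cases, so that the choice of model cannot be influenced by the results.
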